### 2.3. Intervention

The intervention group will complete the *Archena Infancia Saludable* interdisciplinary program for six months. The interdisciplinary research team comprised nutritionists, physicians, PA and sports science professionals, physical education teachers, nurses, and psychologists. The investigators responsible for carrying out the intervention program will not participate in data collection or statistical analysis, so they will not be aware of the participants’ group assignment.

The *Archena Infancia Saludable* project will focus on two fundamental pillars: 24-h movement behaviors and MedDiet. Some examples of the contents of the intervention program are shown in Figure 2. The project will mainly focus on the relationship between parents/guardians and their children. Furthermore, the program includes a behavioral approach (i.e., nutritional education), which encourages the responsibility among all the participants to maintain healthy behavioral changes over the long term [19,34].

The nutritional approach will follow the MedDiet model [13]. We will not impose any caloric restriction since we aim to establish a healthy diet based on the MedDiet [14,25]. Concerning the 24-h movement behaviors, parents/guardians will be told to encourage their children to adopt an active lifestyle with a daily equilibrium of PA, sedentary behavior, and sleep that will support their healthy development [1]. Dietary and 24-h movement behavior changes in schoolchildren will be based on healthy lifestyle education for parents/guardians by infographics, video recipes, information pills, and videos. The contents of these materials have been created by the research team following international and national guidelines for PA [1,35,36], sedentary behavior [1], sleep duration [1,37], MedDiet [38], and healthy eating guidelines [39,40].

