The intervention will be performed by the communication application for schools TokApp (TokApp Online S.L., Vigo, Spain). All the contents of the intervention programs will be delivered online. In line with our hypothesis, only parents/guardians will receive the contents of the intervention. We will try to verify whether intervening in parents/guardians has an impact on 24-h movement behaviors and adherence to the MedDiet in their children. Thus, parents/guardians will receive three different contents weekly (i.e., infographics, video recipes, information pills, or videos) related to 24-h movement behaviors (i.e., PA, sedentary behavior, sleep duration) or MedDiet. In addition, each launched content will be available until the end of the intervention for those who have not been able to view it at the time of its launch. To not discriminate participants from the control group, all project materials will be offered to parents/guardians allocated to the control group at the end of the intervention phase as well. The researchers responsible for sending the contents of the intervention program through the communication application TokApp will not participate in data collection or statistical analysis after the intervention.

The length of the intervention (24 weeks during a school-academic year) falls within the time range used in the prior RCTs conducted on this topic (i.e., 20 weeks [41] and 60 weeks [42]). It has been previously described that when an intervention program is delivered, it can have a compensatory effect, so that participants discontinue other physical activities that they would normally have done otherwise. To address this issue, we will assess PA using activity monitors (i.e., accelerometers) for seven days at two different times during the study: at baseline and postintervention. Finally, any adverse effects will be documented and reported with trial outcomes.

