### 2.4. Strategies to Enhance Adherence to the Intervention Program

Parents/guardians will receive a verbal invitation to take part in the study intervention program and to refer to all the assessments and contents. They will receive a reminder if they have not viewed the contents sent after one week. Our goal will be that parents/guardians engage in at least 80% of the weekly content, which will be considered a successful attendance rate. This evaluation will be possible because the communication application TokApp allows us to know the interaction with the content sent. However, we will encourage the schoolchildren and their families to visualize all contents weekly whenever possible.

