### 2.6. Variables

The complete set of primary, secondary, and tertiary outcomes will be assessed twice, at the time of enrollment and after the 24-week healthy lifestyle program. The measurements will be performed at school by evaluators previously trained to standardize the measurements and blinded to the group in which participants will be allocated. A summary of all the variables that will be examined in the *Archena Infancia Saludable* project is provided in Table 1.

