##### 24-h Movement Behaviors (Self-Reported)

Physical activity will be measured using a self-report questionnaire called the Youth Activity Profile—Spain (YAP-S) [46] aimed at assessing physical activity levels and sedentary behaviors in children. The questionnaire was designed to be completed by the children themselves and involves recalling activities from the past seven days. Screen time will be measured in children by asking their parents/guardians about the amount of time the children spend engaged in sedentary screen-based activities as follows: “Approximately, how much time does your child typically spend in front of a screen (on daily average), including computer, tablet, television, videos, video games or cell phone screen?”. The parents or guardians will be asked separately about screen time on weekdays and weekends. Specifically, they will be asked about the average daily amount of time their child spends in front of a screen. To calculate an overall screen time score, the responses to the three questions (two for the weekend and one for weekdays) will be added together after weighting. Sleep duration will be measured by asking parents/guardians about their child’s bedtime and wake-up time separately for weekdays and weekends as follows: “What time does your child usually go to bed?” and “What time does your child usually get up?”. The average daily sleep duration will be computed for each participant by adding together the average nocturnal sleep duration on weekdays (multiplied by 5) and the average nocturnal sleep duration on weekends (multiplied by 2) and then dividing the total by 7. In addition, two additional questions will be asked about *siesta* habits. First, parents/guardians will be asked if their child usually takes a *siesta*, with options of yes or no. Second, parents/guardians will be asked about the duration of the child’s *siesta*, with options ranging from 0–15 min to 120 min or more. A *siesta* is a customary short nap that is usually taken in the early afternoon, typically following the midday meal, and is prevalent in countries with hot weather conditions, such as those found in the Mediterranean area. The school schedule for all schoolchildren is from 09:00 a.m. to 14:00 p.m., which allows time for children to take a *siesta* after this period.

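### Section 2.3 says delivery staff will not know allocation, which the delivery procedures rule out; blinded evaluators do not protect primary outcomes that the treated parents report

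*Protocol article*

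**What the plan says.** Protocol article, section 2.3 (Intervention), says: "The investigators responsible for carrying out the intervention program will not participate in data collection or statistical analysis, so they will not be aware" of group assignment. The same section sets out delivery: researchers send three items a week through the TokApp application, and "only parents/guardians will receive the contents of the intervention". Controls wait: "all project materials will be offered to parents/guardians allocated to the control group at the end of the intervention phase as well". Section 2.2.1 (Procedure) confirms this by placing the control group's access in the fourth and last phase.

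Section 2.4 adds follow-up of individual parents: "They will receive a reminder if they have not viewed the contents sent after one week". The application shows the team how parents interact with what was sent, and the target is engagement with at least 80% of weekly content.

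Blinding at assessment is stated twice. Section 2.2.4 says data collectors will not know the group at either measurement, and section 2.6 describes the evaluators as "blinded to the group in which participants will be allocated". Nothing says that parents are blinded.

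Section 2.6.1 (Primary Outcomes) contains both accelerometer measures of physical activity, sedentary time and sleep duration, and reported measures. Among the latter: "Screen time will be measured in children by asking their parents/guardians about the amount of time the children spend engaged in sedentary screen-based activities". Questionnaire sleep duration and siesta habits also come from the parent. The YAP-S is completed by the child, and Table 1 lists KIDMED as self-reported by schoolchildren.

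**The concern.** There are two linked problems.

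First, the blinding statement is wrong as written. Keeping delivery staff out of measurement and analysis helps to keep assessors and analysts from learning the allocation. It does nothing to hide the allocation from the people who deliver. Left alone, the statement would carry a blinding claim into the trial report that the design cannot support.

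Second, a blinded evaluator does not help when the informant knows the arm. Intervention parents get six months of material on sedentary behaviour and sleep, built on guidelines that the Introduction quotes as at most 120 minutes of recreational screen time a day and 9–11 hours of sleep for children. They are then asked how long their child spends at a screen and when the child goes to bed and gets up. A parent who has learned the target may answer closer to it without any change in the child. Any such bias would probably favour the intervention. Section 2.5.2 models each dependent variable separately at p ≤ 0.05, so a difference on a parent-reported measure alone could be read as meeting the primary objective.

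**Working it through.** **Can delivery staff be unaware of allocation?** Set the procedures side by side.

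1. During the six months only one arm receives content (section 2.3: "The intervention group will complete the" programme).
2. Researchers send it through TokApp, so someone must address it to the allocated parents.
3. Viewing is tracked and non-viewers are reminded after one week (section 2.4), so someone must work through the list of intervention parents.
4. Controls receive nothing until the intervention phase has ended (sections 2.2.1 and 2.3).

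Steps 1 to 4 mean that the delivery list is the allocation list. Later in section 2.3 the same separation of roles is described for those who send the content, with no claim that they are unaware of allocation. That later wording is consistent with the procedures; the quoted claim is not.

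**Which primary measures depend on an unblinded informant?**

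| Measure (section 2.6.1, Table 1) | Source | Device counterpart |
|---|---|---|
| Physical activity, sedentary time | Accelerometer; YAP-S (child) | Yes |
| Sleep duration | Accelerometer; parent | Yes |
| Recreational screen time | Parent only | None |
| Siesta | Parent | None listed |
| MedDiet adherence (KIDMED) | Child | None |

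Screen time is the guideline component most exposed. Sleep duration is exposed only in its questionnaire form.

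**The plan's own sample size.** Inputs from section 2.5.1: Zα = 1.960, Zβ = 0.842, d = 0.5, SD = 1.0, equal arms, mean cluster size 1.2, within-cluster correlation 0.5, 10% drop-out.

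- N₀ = (1/0.5 + 1/0.5) × (1.960 + 0.842)² / 0.5² = 125.6
- Design effect = 1 + 0.5 × (1.2 − 1) = 1.1, so N₁ = 125.6 × 1.1 = 138.2
- After drop-out: 138 / 0.9 = 153.3, which agrees with the stated 153

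The sample size is not in dispute. It supplies the precision for the next step.

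**Illustration of what a reporting shift would do.** The documents give no size for such a shift, so the between-arm shift b (in SD units) is an assumption, shown over a range. The true effect is set to zero.

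- Effective N = 138 / 1.1 = 125.5
- Standard error of the standardised difference = √(4 / 125.5) = 0.179
- Probability of p ≤ 0.05 = 1 − Φ(1.960 − b/SE) + Φ(−1.960 − b/SE)

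| Assumed shift b (SD) | Probability of p ≤ 0.05 |
|---|---|
| 0 | 5% |
| 0.1 | 8.7% |
| 0.2 | 20% |
| 0.3 | 39% |
| 0.5 | 80% |

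The last row equals the planned power: a shift as large as the design effect size would be declared significant as often as a real effect. The formula is a simple two-group comparison. The planned repeated-measures mixed models would change the figures somewhat.

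**The case against.** The best defence is that the error in section 2.3 has no analytic consequence by itself. Delivery staff are kept out of data collection and analysis, and data collectors are blinded. Informant bias would exist even if the sentence were correct, and it is a limitation of any parent-directed education trial. The article is also open about it: the relevant heading says self-reported, and Table 1 marks screen time as proxy-reported. Accelerometry, the main safeguard, is already planned and comes first among the primary outcomes. All of this stands, and it limits the weight of the point. It does not make the blinding statement true, and no unseen analysis plan could.

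A second defence is that the ranking of measures and the rule for claiming success are often left to an analysis plan that is not shown. That is fair. The article does not state that reported and device measures count equally; it lists both as primary without ranking them. The case for ranking is therefore a design recommendation, not a contradiction.

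A reader might go further and infer that most primary outcomes are compromised, or that only intervention parents can misreport. The documents do not support either. YAP-S and KIDMED come from the child, while content is sent to parents; section 2.4 does encourage children to view it, so some exposure remains, but it is less direct. Control parents answer the same questions and can also give socially desirable answers. What they lack is trial content prompting them.

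**Conclusion.** The point holds in two parts of different weight. The statement that delivery staff will not know allocation is incorrect on the article's own procedures and needs correcting. Parents' awareness is not stated in so many words, but it follows from weekly content in one arm and delayed content in the other.

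Evaluator blinding consequently does not protect parent-reported screen time and questionnaire sleep duration. This is a risk of bias, probably towards benefit, and not a demonstrated effect. It would be tempting to read the 20% to 39% figures as this trial's false-positive rate. They are not: they follow from an assumed shift of 0.2 to 0.3 SD that no document supports, and at 0.1 SD the figure is about 9%. Accelerometer outcomes and the sample size are unaffected.

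**What to change.** 1. Reword the blinding statement in section 2.3: delivery staff and parents are not blinded; data collectors are; delivery staff take no part in data collection or analysis. Claim that the analyst is blinded only if that is actually adopted, since the article does not say so.
2. In section 2.6.1, name the accelerometer measure as the primary measure of physical activity, sedentary time and sleep duration, with YAP-S and parent-reported sleep as supportive.
3. Keep recreational screen time as a component of the 24-h movement objective, because it is one of the three guideline components and has no device measure. Report it as an unblinded proxy outcome that does not alone support a claim of benefit on movement behaviours.

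KIDMED needs little change: Table 1 already has the child as respondent, and section 2.6 already places measurement at school with blinded evaluators.

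The cost is wording and outcome ordering, as every measure is already collected. The downside is that reported physical activity and sleep lose co-primary standing. Dropping screen time from the primary set would be a larger loss and is not needed.

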### 2.4. Strategies to Enhance Adherence to the Intervention Program

Parents/guardians will receive a verbal invitation to take part in the study intervention program and to refer to all the assessments and contents. They will receive a reminder if they have not viewed the contents sent after one week. Our goal will be that parents/guardians engage in at least 80% of the weekly content, which will be considered a successful attendance rate. This evaluation will be possible because the communication application TokApp allows us to know the interaction with the content sent. However, we will encourage the schoolchildren and their families to visualize all contents weekly whenever possible.

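### Section 2.4 encourages the children themselves to view content that Section 2.3 sends to parents only, so an effect could not be attributed to parents alone

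*Protocol article*

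**What the plan says.** Section 2.3 (Intervention) names the recipients and links the choice to the hypothesis: "In line with our hypothesis, only parents/guardians will receive the contents of the intervention". The next sentence gives the purpose: "We will try to verify whether intervening in parents/guardians has an impact on 24-h movement behaviors and adherence to the MedDiet in their children". Earlier in the same section the mechanism is put the same way: "Dietary and 24-h movement behavior changes in schoolchildren will be based on healthy lifestyle education for parents/guardians". The Discussion (Section 3) also presents the programme as directed at parents, with improvement looked for in their children.

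Section 2.4 (Strategies to Enhance Adherence to the Intervention Program) sets an engagement target for the adults: "Our goal will be that parents/guardians engage in at least 80% of the weekly content". It says this can be checked because "the communication application TokApp allows us to know the interaction with the content sent". It then adds that "we will encourage the schoolchildren and their families to visualize all contents weekly whenever possible". The children are named there separately from their families, and the encouragement covers all contents, every week.

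**The concern.** Infographics and videos work by being viewed. If the study team prompts children to watch them, the children are exposed to the material directly, whoever holds the app account. The trial has two arms, programme and delayed programme, and no arm in which only the parents see the content. A benefit in the children could then come from what parents did, from what the children saw, or from both.

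Two things are at stake.

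- **Interpretation.** The article wants to speak about intervening in parents, and a mixed route weakens that reading. The Discussion calls this a pilot meant to consolidate the programme for the other schools in the municipality, so those who scale it up need to know whether children are an intended audience.
- **Measurement.** Some primary outcomes are answered by the children. Children who have seen material stating the desired behaviours may report more of them. Controls receive the material only after the post-intervention measurements (Section 2.2.1, fourth phase), so this would affect one arm only.

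**Working it through.** The point rests on comparing sections, with only a little arithmetic.

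**1. Who is exposed**

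| Place | Statement, paraphrased | Role of the child |
|---|---|---|
| 2.3 | Content goes to parents/guardians only, as the hypothesis requires | Not a recipient |
| 2.3 | Change in children rests on educating parents | Indirect |
| Discussion | Programme directed at parents, benefit sought in children | Indirect |
| 2.4 | Children are encouraged to view everything weekly | Direct viewer |

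Three statements agree, and the encouragement in Section 2.4 departs from them. Section 2.3 concerns who is sent the content and Section 2.4 who views it, so the sentences can be literally compatible. They still describe different exposures for the child.

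**2. What the comparison estimates under each reading**

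- Children do not view the content: difference between arms = effect through parents.
- Children are prompted to view it: difference between arms = effect through parents and direct viewing combined.

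In both cases the intention-to-treat contrast (Section 2.5.2) is a valid estimate of the effect of being assigned the programme as delivered. Only in the first case can that effect be credited to parents alone.

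**3. Whether the routes can be told apart**

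- The 80% target is defined for parents/guardians.
- The app shows interaction with the content sent. The article does not say that it distinguishes a parent from a child using the same account.
- No separate measure of child viewing is described, and no arm isolates one route.

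The data as described therefore cannot show how much direct viewing took place.

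**4. Amount of content**

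3 contents per week (Section 2.3) × 24 weeks = 72 items. This is the number sent to a family. It says nothing about how many a child views or what share of an effect that would explain.

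**5. Which primary outcomes are open to reporting bias (Section 2.6.1 and Table 1)**

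| Outcome | Reported by | Open to desirable answering by the child? |
|---|---|---|
| Activity, sedentary time and sleep by accelerometer | Device | No |
| YAP-S | Child | Yes |
| KIDMED | Child | Yes |
| Screen time and sleep by questionnaire | Parent | No, but the parent has received the same messages |

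**6. Sample size (Section 2.5.1)**

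N₀ = 4 × (1.960 + 0.842)² / 0.5² = 125.6, or 126. With the design effect 1 + 0.5 × (1.2 − 1) = 1.1, 125.6 × 1.1 = 138.2, or 138. With 10% drop-out, 138 / 0.9 = 153.3, against the stated 153. None of these inputs depends on who views the content, so the sample size is the same under either reading.

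**The case against.** The strongest reply is that there is no contradiction. A parent can be the only person sent a video recipe and then watch it with the child. Section 2.3 says the project centres on the relationship between parents and children, so shared viewing may be one way of intervening through parents. The objectives in the Abstract and Introduction concern the effect of a lifestyle intervention on children. They do not exclude child viewing and do not define a mediation effect. On that view the trial asks about a total effect and estimates it.

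Much of this stands, and it rules out several stronger readings that a reader might infer:

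- *That the two sections cannot both be true.* Being sent material and viewing it are different things.
- *That the trial could not answer its question about parents.* The comparison still bears on whether a programme delivered through parents changes child behaviour. Only attribution to parents alone is weakened, and only as far as children actually watch.
- *That child viewing would go wholly unrecorded.* A child using the parent's account might be logged. What the article supports is that no separate child measure is described.
- *That the primary outcomes as a whole would be biased.* The accelerometer outcomes are not exposed to this. Parents who have been taught the messages also proxy-report, and may pass the desired answers on to their children, so some reporting bias would exist under strict parent-only delivery.

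The reply does not dispose of Section 2.3 making parent-only receipt part of the hypothesis while Section 2.4 makes the team an active promoter of viewing by children. Prompting by the study team is more than incidental viewing at home. Nor is this a detail that a condensed article leaves to a fuller document, because both statements are printed and they bear on what the intervention is.

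**Conclusion.** The concern holds in a limited form. The article is unclear on whether children are meant to see the content directly. If Section 2.4 is carried out, a difference between arms combines parent-mediated change with direct exposure of the child, and the effect could not be attributed to intervening in parents alone. The estimate for the programme as delivered remains valid.

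No numerical size can be given. The share of any effect due to direct viewing is not known and could not be estimated from the data as described. Added reporting bias is possible on KIDMED and YAP-S, of unknown size and on top of what parent-only delivery would already produce.

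This rests on two assumptions: that the encouragement is actually given, and that at least some children respond to it. If no child views the content, the parent-only interpretation is intact.

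**What to change.** Reconcile Sections 2.3 and 2.4 before the start, in one of two ways:

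1. Limit the encouragement in Section 2.4 to parents/guardians, which keeps the parent-only question; or
2. Keep the encouragement, and state the hypothesis and conclusion as the effect of a programme offered to families through parents.

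Optionally, add one post-intervention question asking parents how often the child viewed the content, and report the answer beside the primary result. It would show whether direct exposure was rare or common. It would not separate the two routes causally, because viewing is not randomised.

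The cost is an edited sentence, or a restated hypothesis and conclusion, plus one questionnaire item if that is wanted. The downside of the second option is a narrower conclusion, since the trial would no longer speak about parents alone. Neither option changes the sample size or the planned comparison.
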